## FLOW CHART

[figure not shown]

FCM= Ferric Carboxymaltose Ferinject ®)

[figure not shown]

[name]; PhD; FASN.  
Professor of Medicine University of Buenos Aires  
Chief of Nephrology.  
Hospital Alemán, [name]  
Buenos Aires (1118)- Argentina  
[contact]  
[contact]  
Mobile [contact]  
E-mail: [contact]

## **POPULATION AND SAMPLE**

### *Population*

The reference population will be patient resident adults in Buenos Aires who are covered by any regime of social security, taking as population of study those attended in the hospital who fulfil the exclusion and inclusion criteria.

### *Study Sample*

Thirty consecutive patients who fulfilled the inclusion and exclusion criteria

## **VARIABLES**

### *1-Dependent Variables*

- Heart rate
- Breath rate
- Blood pressure
- Severity of the Anemia: According to the classification established by the WHO.
- Hemoglobin: substance inside erythrocytes consisting of a protein that binds iron
- Hematocrit: Proportion of erythrocytes in plasma
- Mean Corpuscular Volume (MCV): cellular index that reflects erythropoiesis.
- Serum Ferritin
- Percentage of transferrin saturation
- Creatinine Clearance
- Proteinuria
- Amount of Erythropoietin.
- Number of transfusions
- Number of hospitalizations
- Death
- Cause of Death
- Adverse Events: Appearance of adverse reactions in the organism with the treatment administered. Among others: nausea, vomiting, headache, diarrhea, allergy and hypotension.

### *2-Independent variables*

- CV Drugs (It includes Angiotensin Converting Enzyme Inhibitors and Antagonist of the Angiotensin II receptor type 1).

[figure not shown]

[name]; PhD; FASN.  
Professor of Medicine University of Buenos Aires  
Chief of Nephrology.  
Hospital Alemán, [name]  
Buenos Aires (1118)- Argentina  
[contact]  
[contact]  
Mobile [contact]  
E-mail: [contact]

## **DATA COLLECT METHODOLOGY**

The application of all forms will be done based on a primary source, i.e. the information will be taken by the investigators through direct evaluation of the patients by physical examination and the results from their blood and serum sample analysis.

- 1: Initial clinical and laboratory evaluation of the patient by means of direct observation and the transcription of the obtained results of laboratory as a point to begin. (Appendix 1)
- 2: Clinical and laboratory evaluation of the follow-up of the patient by means of direct observation and the transcription of the obtained results of laboratory during the different moments in the follow-up. (Appendix 1)
- 3: Record of symptoms and side effects. It will be record by the investigator in every visit (Appendix 1)

## **DATA COLLECT TECHNIQUES**

### *Pertinent authorization formalities*

The investigation project will be submitted to the ethics and investigation committees of the Hospital Alemán (Deutches Hospital) with the aim of obtaining the corresponding permissions for the accomplishment of the study.

### *Recruitment and training of the personnel*

It will be supported by the principal and co-investigators, who will participate in the initial evaluations and in the follow-up of the patients. Before initiating the study, an instruction will be given as how to fill the forms.

### *Data sources and data collecting procedures*

In order to collect the data, the direct observation through clinical examination and blood sample analysis and serum will be used. The registry of the data obtained will be done in the corresponding forms.

[figure not shown]

[name]; PhD; FASN.  
Professor of Medicine University of Buenos Aires  
Chief of Nephrology.  
Hospital Alemán, [name]  
Buenos Aires (1118)- Argentina  
[contact]  
[contact]  
Mobile [contact]  
E-mail: [contact]

## **STATISTICS**

All statistical analyses will be processed through GraphPad Prism version 4.0 (GraphPad Software, Inc. San Diego, CA). Initially, a descriptive statistic of the sociodemographic, clinical and laboratory characteristics will be performed of all the participant patients of the study, directed to describe patient population. Then, calculation of absolute frequencies, proportions, measures of central tendency and dispersion of the involved variables will be performed. When evaluating parameters with a Gaussian distribution, comparisons will be carried out using t-test. For those parameters with a non-Gaussian distribution, comparisons will be performed by non-parametric methods using the Wilcoxon rank sum test. Values will be expressed as mean  $\pm$  SD, and  $p < 0.05$  will be considered significant.

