## **OBJECTIVE**

### *Primary:*

- To determine possible reduction in ESA requirements after intravenous 1g Ferric Carboxymaltose (FERINJECT ®) administration in patients with CKD in pre-dialysis stage, who were under a monthly EPO treatment and continuous oral iron therapy during the previous six months, in order to maintain a Hb value according to international recommendations.

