### *Secondary:*

- To assess the number of hospitalizations pre (six months) and post (six months) intravenous 1g Ferric Carboxymaltose (FERINJECT ®) administration in patients with CKD in pre-dialysis stage.
- To record the need for transfusion pre (six months) and post (six months) intravenous 1g Ferric Carboxymaltose (FERINJECT ®) administration in patients with CKD in pre-dialysis stage.
- To evaluate renal function as measured by Creatinine clearance and proteinuria of 24 hours, pre (six months) and post (six months) intravenous 1g Ferric Carboxymaltose (FERINJECT ®) administration in patients with CKD in pre-dialysis stage.
- To analyze the number of adverse reactions and complications due to intravenous 1g Ferric Carboxymaltose (FERINJECT ®) administration in patients with CKD in pre-dialysis stage.

[figure not shown]

[name]; PhD; FASN.  
Professor of Medicine University of Buenos Aires  
Chief of Nephrology.  
Hospital Alemán, [name]  
Buenos Aires (1118)- Argentina  
[contact]  
[contact]  
Mobile [contact]  
E-mail: [contact]

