## **STUDY DESIGN**

- Prospective study to 6 months with a single branch of patients who are treated with monthly EPO therapy together with oral iron for at least the last six months before the study and met inclusion criteria.
- From CKD database are randomly selected 30 patients. After signing an informed consent form in duplicate and with witness, duly authorized by the Committee on Education and Research institutions, all patients will receive intravenous 1g Ferric Carboxymaltose (FERINJECT ®) in one dose of 1000 mg on the recommendation of the product.
- On a monthly basis after intravenous 1g Ferric Carboxymaltose (FERINJECT ®) the administration, all patients will be controlled dosage of Hb by HemoCue, in order to dispense the EPO to maintain a baseline Hb level.
- Monthly checks will be carried to register: vital signs and weight control, and record of adverse reactions linked to 1g Ferric Carboxymaltose (FERINJECT ®) administration, registration HemoCue results.
- Before FERINJECT treatment and then every two months, all patients underwent blood control that includes: complete blood count haematimetric indexes, platelet count, serum iron, serum ferritin, TSAT, CRP, urea, creatinine, liver function tests).
- There will be collection of 24-hour urine to measure Creatinine Clearance and proteinuria at baseline and at the end of the study.

[figure not shown]

[name]; PhD; FASN.  
Professor of Medicine University of Buenos Aires  
Chief of Nephrology.  
Hospital Alemán, [name]  
Buenos Aires (1118)- Argentina  
[contact]  
[contact]  
Mobile [contact]  
E-mail: [contact]

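### The non-parametric test named for the pre/post comparisons is one for independent samples, although both values come from the same patients; the t-test is not stated to be paired.

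*Protocol*

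**What the plan says.** The STUDY DESIGN section describes a "Prospective study to 6 months with a single branch of patients", and the sample is 30 ("From CKD database are randomly selected 30 patients"). The primary objective is "To determine possible reduction in ESA requirements after intravenous 1g Ferric Carboxymaltose", in patients already on EPO and oral iron for the preceding six months. The first secondary objective reads "To assess the number of hospitalizations pre (six months) and post (six months" months), and the transfusion and renal-function objectives have the same before/after form. The design section also calls for "Creatinine Clearance and proteinuria at baseline and at the end of the study".

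On testing, the STATISTICS section has two branches. For the first: "When evaluating parameters with a Gaussian distribution, comparisons will be carried out using t-test". For the second, covering non-Gaussian parameters: "comparisons will be performed by non-parametric methods using the Wilcoxon rank sum test". Significance is set at p below 0.05. The protocol mentions neither pairing nor the signed-rank test, and it defines no second patient group.

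**The concern.** In a single-arm study each patient's own pre-treatment period is the only comparator. The rank sum test treats the 30 pre values and the 30 post values as if they came from 60 unrelated people. It leaves between-patient variation in the error term, which a within-patient analysis would remove.

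The non-parametric branch may well receive the primary variable. Three of the six rows in the protocol's table of measures after treatment give no EPO, so post-treatment EPO could contain many zeros. Hospitalization and transfusion counts, ferritin and proteinuria are also likely to be skewed. What is at stake is whether 30 patients can show a moderate reduction in ESA requirement that is really there.

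**Working it through.** The protocol states no power, effect size, SD or correlation, so it has no figure of its own to reproduce. The check compares paired and unpaired analysis of the same 30 pairs.

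**Inputs from the Protocol:** one arm and n = 30 (STUDY DESIGN); significance level 0.05 (STATISTICS).

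**Assumptions:** two-sided testing; equal SD before and after; pre/post correlation ρ of 0, 0.3, 0.5 or 0.7; a shift of 0.5 SD for the power comparison.

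**Step 1: standard errors, in SD units.**
- Unpaired: √(2/30) = 0.258.
- Paired: √(2(1−ρ)/30), which is 0.183 at ρ = 0.5.
- Ratio: 1/√(1−ρ) = 1.00, 1.20, 1.41 and 1.83 at the four correlations.

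**Step 2: actual type I error of an unpaired test, normal approximation.** 2·[1 − Φ(1.96/√(1−ρ))] gives 0.050, 0.019, 0.0056 and 0.0003.

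**Step 3: simulation of the rank tests.** 20,000 replicates per setting, normal data:

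| Assumed ρ | Type I error, rank sum | Type I error, signed-rank | Power at 0.5 SD, rank sum | Power at 0.5 SD, signed-rank |
|---|---|---|---|---|
| 0 | 0.0478 | 0.0507 | 0.45 | 0.45 |
| 0.3 | 0.0200 | 0.0504 | 0.45 | 0.59 |
| 0.5 | 0.0074 | 0.0455 | 0.44 | 0.74 |
| 0.7 | 0.0011 | 0.0495 | 0.43 | 0.92 |

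The rank sum test would be applied to non-Gaussian variables, so log-normal data were also tried. The pattern is the same. Rank sum type I error is 0.051, 0.023, 0.007 and 0.001. Its power is 0.43 to 0.45, against 0.42, 0.56, 0.69 and 0.89 for the signed-rank test. Data with many zeros or ties were not simulated.

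**Step 4: one observed result analysed both ways.** Take an observed shift of 0.5 SD, normal approximation.
- Unpaired: z = 0.5/0.258 = 1.94, p = 0.053 whatever ρ is.
- Paired at ρ = 0.5: z = 0.5/0.183 = 2.74, p = 0.006.
- Paired at ρ = 0.3 and 0.7: p = 0.021 and 0.0004.

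From ρ = 0.3 upwards, the two analyses fall on opposite sides of the protocol's 0.05 threshold.

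**Step 5: shift detectable with 80% power at ρ = 0.5.**
- Paired: (1.96 + 0.84) × 0.183 = 0.51 SD.
- Unpaired: 1.96 × 0.258 + 0.84 × 0.183 = 0.66 SD.

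**Step 6: direction.** With positive correlation the error is conservative. Only a negative correlation raises the type I error: the simulated rank sum rate is 0.079 at ρ = −0.3.

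**The case against.** Several points in the protocol's defence are fair.

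- **The t-test.** A reader might infer that the whole study will be analysed as two independent groups. The text does not support that. An unqualified t-test can be the paired one, and leaving the variant to a later plan is ordinary. Only the rank sum branch is wrong as written.
- **Direction.** A reader might expect false claims of benefit. With positive correlation the reverse holds: p-values are too large.
- **Correlation.** The protocol gives none, and it may be low for some variables. Entry Hb is restricted to 11 to 12 g/dl, and stopping EPO can weaken the link with the earlier dose. At ρ = 0 nothing is lost.
- **Size of effect.** Rank sum power does not collapse as the correlation rises. For a fixed 0.5 SD shift it is flat, while paired power climbs. An apparent collapse comes from shrinking the raw effect to hold paired power constant. For a 1 SD shift the rank sum test has power of about 0.96 or more at every correlation from 0 to 0.7, so a large ESA reduction would still be found.
- **Scope.** Not every objective is paired. The adverse-reaction objective has no pre-treatment period. Cardiovascular drugs are listed as an independent variable, and a comparison by drug use would be between groups, where a rank sum test fits.
- **Pilot status.** This is a small pilot, and the right test could be run later on the same data.

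All of this limits the point but does not remove it. The protocol names a specific test, that test does not match its pre/post comparisons, and no other section corrects it. Changing the test after the results are seen would be a post hoc choice. How values are summarised, whether confidence intervals are given and how the ESA endpoint is defined are separate or later matters, and the point does not rest on them.

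**Conclusion.** The point holds for the rank sum test in the pre/post comparisons of ESA requirement, hospitalizations, transfusions and renal function. For the t-test it holds only as a missing word. The consequence is lost power. It is nil at zero correlation, moderate at 0.3 (power 0.45 against 0.59 for a 0.5 SD shift) and large from about 0.5 (0.44 against 0.74). These sizes rest on assumed correlations, equal SDs, two-sided testing and normal data, with log-normal data giving a similar picture. The documents do not support a claim that false positives are likely or that every analysis in the study is affected.

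**What to change.** In the STATISTICS section, for the pre/post comparisons:

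- replace the Wilcoxon rank sum test with the Wilcoxon matched-pairs signed-rank test;
- replace t-test with paired t-test;
- state that the choice between the two rests on the distribution of the within-patient differences.

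If a between-group comparison is intended, for example by cardiovascular drug use, say so and keep the rank sum test for that use only.

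The cost is one paragraph. Both tests are standard, and no extra patients, visits or measurements are needed.

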## **ETHICAL ISSUES**

The following issues will be considered:

**A-Protection of the professional secret.** The identification data of the participant patients will be replaced assigning a code to them at the time of entering the study

**B-Informed Consent:** Once obtained the reference population, there will be an invitation to participate in the study to the patients who fulfil the inclusion and exclusion criteria already mentioned. To those interested there will be an explanation of the study objectives and an Informed Consent will be given which includes information about the importance of the present investigation, the characteristics of the study and the benefits and potentials risks that they will be exposed when participating in the project. If the patient is illiterate, an acceptable legal representative will have to sign the informed consent.

**C-During the accomplishment of the study,** every 4 weeks, partial information will be taken to evaluate the treatment effectiveness and its safety allowing the detection of hazardous situations that can risk the health conditions of the participants in the study.

[figure not shown]

[name]; PhD; FASN.  
Professor of Medicine University of Buenos Aires  
Chief of Nephrology.  
Hospital Alemán, [name]  
Buenos Aires (1118)- Argentina  
[contact]  
[contact]  
Mobile [contact]  
E-mail: [contact]

### **Timelines**

- a. FPFV: 14/03/2011
- b. LPFV: 09/11/2012
- c. LPLV: 10/05/2013
- d. FR: 08/07/2013
